## **6 SAFETY**

### **6.1 Adverse Events**

Illnesses present at study entry are considered pre-existing conditions and will be documented as medical history on the CRF provided. All adverse events, including intercurrent illnesses and worsening of pre-existing conditions, must be reported and documented as described below.

#### **6.1.1 Definitions**

An adverse event is any untoward medical event that occurs in a subject or subject administered a pharmaceutical product and that does not necessarily have a causal relationship with this treatment. An AE can therefore be any unfavorable and unintended sign (including abnormal laboratory findings), symptom, or disease temporally associated with the use of a medicinal (investigational) product, whether or not related to the medicinal (investigational) product.

#### **6.1.2 Assessment of Adverse Events**

Volunteered, observed, and elicited reports of adverse events will be recorded. This includes adverse events the subject reports spontaneously, those the investigator observes, and those the investigator elicits in response to open-ended questions at the times indicated on the Schedule of Observations. At each visit, the subject should be asked a non-leading question such as: “Do you feel different in any way since your last visit?” Subjects will also be questioned concerning possible skin reactions according to a specific checklist of possible adverse events.

Each adverse event will be assessed by the investigator with regard to the following categories.

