## **4 STUDY POPULATION**

### **4.1 Inclusion Criteria**

Subjects who meet all of the following criteria are eligible for this study:

- 1) Fulltime healthcare providers, medical doctors, physician assistants, nurses or other HCPs involved in active patient care or administration of patient care (Hospital Administration).
- 2) 18 years or older.
- 3) Have treated COVID-19 patients or working at locations where COVID-19 patients are being treated.
- 4) Willing and able to complete both baseline and post-testing as noted above.
- 5) If being treated with psychoactive medications, the maintenance of a stable regimen for at least two months before enrollment.
- 6) In the non-control group, willing and able to dedicate the time to learning the Transcendental Meditation technique and practice it twice daily for approximately 20 minutes.

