### **4.2 Exclusion Criteria**

Subjects who meet any of the following criteria are not eligible for this study:

- 1) Already instructed in the Transcendental Meditation technique.
- 2) Currently unstable psychiatric symptoms as demonstrated by self-report, medical chart, or psychiatric hospitalizations in the past six months.

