### **4.3 Withdrawal and Replacement of Subjects**

Subjects who withdraw consent must be withdrawn from the study. No justification for such a decision is required. Subjects must be withdrawn from the study if the investigator considers it in the best interest of the subject that he/she be withdrawn. Subject must notify the principal investigator in writing at the time of their decision. The reasons for withdrawal must be recorded, if available, on the case report form (CRF) and in the subject's medical records.

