## 5 STUDY PROCEDURE

**Transcendental Meditation (TM):** TM is an effortless technique that produces a state of ‘restful alertness’ associated with a more integrated style of brain functioning. TM will be delivered to participants by certified instructors of the program in a standardized format (see below; also Roth, 2018; Nidich et al., 2018; Schneider et al., 2012). The TM technique is not based on religious or other philosophical beliefs and does not involve major changes to one’s lifestyle. Important advantages of employing TM in research include a standardized and reproducible instruction format, a thorough certification program for instructors, and widespread availability of instructors in North America and in major cities throughout the world.

Two experienced certified TM instructors will conduct the instruction. All certified TM teachers have been extensively trained in the teaching of the TM program, including teaching the initial course of instruction, verifying continued correctness of effortless practice of the technique, and conducting additional follow-up sessions. The same standardized TM course sequence will be used for all study participants.

**Outline of Transcendental Meditation Program:** TM will involve 10 total sessions over 12 weeks. The core training in the TM technique will be done over five sessions. The five core instruction sessions will include: a) Introductory/Preparatory Lecture—review of previous scientific research on the TM program and a discussion of the mechanics and origin of the TM technique; b) Personal Instruction—individual one-on-one instruction in the TM technique (75 minutes); c) First Day of Verification of Correct Practice and Further Instruction (75 minutes-group session); d) Second Day of Verification of Correct Practice—understanding the mechanics of the TM technique from personal experiences (75 minutes-group session); e) Third Day of Verification of Correct Practice—understanding the mechanics of the development of higher human potential and wellness (75 minutes-group session).

Following the initial phase of the intervention (5 sessions), there will be 3 additional group sessions, each 45 minutes’ duration, provided once a month for the remainder of the 3-month intervention period. These sessions will include: a) discussion of personal experiences and verification of correctness of practice of the TM technique, and b) knowledge of the human potential and its relationship to mental and physical health.

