## **6.2 Schedule of Assessments**

Study outcome measures, The Maslach Burnout Inventory (MBI-HSS) for Medical Personnel, Insomnia Severity Index (ISI), Patient Health Questionnaire (PHQ)-9 depression, Generalized Anxiety Disorder (GAD)-7 and the Warwick-Edinburgh Mental Well-Being Scale (WEMWBS) will be assessed at baseline, 2 weeks, 1 month, and 3 months posttest, (+/- 7 days) with change in burnout as the primary outcome. The measures will either be administered in person or virtually). The total duration of the study period will be 3 months.

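### The adverse event checklist in Section 6.1.2 names skin reactions, which do not fit a meditation trial, while psychiatric symptoms have no named targeted query

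*Protocol*

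**What the plan says.** Section 6.1.2 (Assessment of Adverse Events) gives several routes by which an adverse event reaches the record. Events may be volunteered by the subject or observed by the investigator. They may also be elicited, described as "those the investigator elicits in response to open-ended questions at the times indicated on the Schedule of Observations". The open prompt is set for every visit: "At each visit, the subject should be asked a non-leading question such as", followed by an example asking whether the subject feels different since the last one. The section then adds a single targeted element: "Subjects will also be questioned concerning possible skin reactions according to a specific checklist of possible adverse events". No other subject is named for that checklist, and its contents are not reproduced.

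Section 6.1 also makes deterioration of a condition present at entry reportable.

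Section 5 describes the intervention: "TM will be delivered to participants by certified instructors of the program in a standardized format". Controls continue their usual lifestyle.

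On eligibility, Section 4.2 excludes people already taught the technique and, as its only clinical criterion, "Currently unstable psychiatric symptoms as demonstrated by self-report, medical chart, or psychiatric hospitalizations in the past six months". Section 4.1 admits people on psychiatric treatment under a condition: "If being treated with psychoactive medications, the maintenance of a stable regimen for at least two months before enrollment".

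Section 6.2 says the outcome scales "will be assessed at baseline, 2 weeks, 1 month, and 3 months posttest". It lists no adverse event query.

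**The concern.** A targeted query helps when it covers the harms that the intervention or the population makes plausible. Here the only named target is an event type that nothing in the trial would be expected to cause: no drug, topical product or device is given. The area that the protocol itself treats as a clinical risk at entry is left to general prompts once the subject is enrolled.

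What is at stake is recognising and recording harm in individuals. A subject whose mood, anxiety or sleep worsens may not mention it in reply to a general question, and may then not appear in the adverse event record. The withdrawal rule in Section 4.3, "Subjects must be withdrawn from the study if the investigator considers it in the best interest of the subject", also depends on the investigator learning that the subject has worsened.

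**Working it through.** No arithmetic applies. The point is about how events are collected, so the check sets the relevant sections side by side.

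1. **Does anything in the trial explain a skin query?** Section 5 describes instruction sessions and home practice of meditation; the control condition is usual lifestyle. Neither involves skin contact or a product. The answer is no.

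2. **Is the sentence isolated?** No. Section 4.4 refers to a bottle in the numbering sequence. Section 6.1.1 defines an adverse event by administration of a pharmaceutical product. The severity and causality tables in 6.1.2, and Sections 6.1.3 and 6.1.4, refer to study medication. The causality table is headed with the study procedure, but its text judges events against a medication that this trial does not have. The skin sentence fits that pattern, so carry-over from a drug study is the natural explanation. This is an inference; the protocol does not say so.

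3. **Which clinical area does the protocol treat as relevant?** The only clinical exclusion in 4.2 is psychiatric. Section 4.1 sets a stability condition on psychoactive medication. Section 2 describes healthcare workers as prone to burnout, insomnia and depression. All three point to psychological symptoms.

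4. **How can a psychiatric event be captured after entry?** By four general routes: the open question at each visit, a volunteered report, an observation by the investigator, and the duty in 6.1 to report deterioration of an existing condition. None is directed at psychiatric symptoms in particular. No targeted psychiatric query is named in Sections 6.1 to 6.2.

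5. **Do the outcome scales fill the gap?** They measure symptoms at each assessment, but as outcomes. Section 3.1 names the BSI 18, while Section 6.2 names the PHQ-9 and GAD-7 instead, so it is not settled which symptom forms will be completed. Worsening across a group should show in whichever scale is used. That does not put an individual's event into the adverse event record.

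6. **Where is the questioning scheduled?** Section 6.1.2 points to a Schedule of Observations. In the text available, the only schedule is 6.2, which covers outcome scales. A separate table may exist, so this is a cross-reference to tidy and does not show that no query is scheduled; 6.1.2 itself requires the open question at each visit.

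Result: the one named targeted query is aimed at an irrelevant event type, and the relevant area is covered only in general terms.

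**The case against.** The strongest reply is that the open question suits this trial. Asking whether someone feels different invites reports of changed mood, anxiety or sleep, and it does so without suggestion. Volunteered and observed events are recorded too. This stands: it would be wrong to infer that psychiatric harm goes uncaptured, or that a single open question is the only route.

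A second reply is that the checklist is described as covering possible adverse events and is not shown, so it may hold psychiatric items. This also stands as a possibility. A reader might infer that skin is all it contains, and the protocol does not establish that. If it is broader, the sentence describes it badly and still needs correcting.

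A third reply concerns bias. The comparison is with usual lifestyle, and participants know whether they were taught meditation. A prompted symptom list can raise reporting, perhaps unequally between groups. This is a real cost of the remedy, and the fix has to deal with it.

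A reader might also take the lack of a rule turning a worsened score into an adverse event as an error. It is not one: keeping efficacy scores apart from adverse events avoids counting one observation twice and is a defensible choice.

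What the replies do not remove is the sentence itself. It is an operative instruction that spends the protocol's only named targeted query on the wrong area.

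**Conclusion.** The point holds, at minor severity. Section 6.1.2 directs checklist questioning at skin reactions in a trial of meditation, while psychiatric symptoms have no named targeted query and depend on general routes. Psychological harms in individuals may be under-recorded as adverse events.

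The size cannot be derived. The protocol gives no expected event rate and no basis for saying what share general questioning would miss. Figures calculated from the 65 per group would describe any adverse event whatever questions were asked, so they would not measure this fault and none is offered. The analysis of burnout, insomnia, symptoms and well-being is unaffected.

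The conclusion rests on two assumptions: that the unseen checklist is about what its description says, and that psychiatric symptoms are the more relevant area, which follows from the protocol's own eligibility criteria. It does not support a claim that the trial has no psychiatric safety monitoring, or that one group's events would be missed more often than the other's under the present text.

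**What to change.** In Section 6.1.2, keep the open question and ask it first. Replace the skin sentence with a short checklist of new or worsening mood, anxiety, sleep and other psychiatric symptoms, asked in the same words in both groups at 2 weeks, 1 month and 3 months. Mark on the form whether each event was reported before or after prompting, and record prompted and unprompted events separately so that unequal prompted reporting can be seen.

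List the checklist in Section 6.2 and have 6.1.2 refer to that section. In the causality text, and where the relationship is recorded under 6.1.3, replace study medication with the study procedure; otherwise a newly captured psychiatric event would be judged against a drug that does not exist.

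The cost is modest because a checklist is already planned. It needs a protocol amendment, a revised paper worksheet and CRF page, and IRB approval if the change counts as major under Section 8.6. With 130 subjects and three post-baseline assessments, the form would be completed at most 130 × 3 = 390 times, assuming full enrolment and follow-up. The recorded adverse event count will probably rise, and prompted reports may differ between groups for reasons unrelated to harm.

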#### **Serious/Not Serious**

International Conference on Harmonization (ICH) Guidelines and US Federal Regulations define a serious adverse event (SAE) as any untoward medical occurrence that at any dose:

- Results in death.
- Is life-threatening. This means that the subject is at risk of death at the time of the event; it does not mean that the event hypothetically might have caused death if it were more severe.
- Requires or prolongs hospitalization (hospitalization defined as  $\geq 24$  hours).
- Results in persistent or significant disability or incapacity.
- Is a congenital anomaly or birth defect.
- Important medical events that may not be immediately life-threatening or result in death or hospitalization, but that may jeopardize the subject or require intervention to prevent one of the above outcomes, usually should also be considered serious. Events are considered serious if they result in life threatening events, death, genetic abnormality, persistent disability, or prolonged hospitalization. Examples include pregnancy, allergic bronchospasm requiring treatment at home or in the emergency room, and blood dyscrasias or convulsions not resulting in hospitalization. Medical and scientific judgment should be used to determine whether such events should be considered serious.
- Pregnancy should always be considered as a serious adverse event. As such, pregnancy should be recorded on the adverse event page of the CRF and a serious adverse event form completed and submitted as described.

Serious adverse events will be reported to the IRB/sponsor no more than 7 business days from the beginning of the event.

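### The clock for reporting serious adverse events starts at onset rather than at site awareness, so most such events first learned of at a visit are already past the limit and then have no deadline

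*Protocol*

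**What the plan says.** Under Serious/Not Serious in Section 6.1.2, the protocol gives one time limit: "Serious adverse events will be reported to the IRB/sponsor no more than 7 business days from the beginning of the event". No other section starts a clock when the site becomes aware.

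Section 6.1.2 accepts three routes by which an event can come to light: "This includes adverse events the subject reports spontaneously, those the investigator observes, and those the investigator elicits in response to open-ended questions". On elicitation it says: "At each visit, the subject should be asked a non-leading question". The sample question asks about changes since the previous visit, so it looks back over the whole gap between visits.

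Section 6.2 sets the timing of the outcome measures, which "will be assessed at baseline, 2 weeks, 1 month, and 3 months posttest, (+/- 7 days) with change in burnout as the primary outcome". Section 5 gives the meditation arm a core course and then monthly group sessions. It describes no further contact for the control arm, which continues as usual.

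Pregnancy is included without exception: "Pregnancy should always be considered as a serious adverse event". It follows the same route: "pregnancy should be recorded on the adverse event page of the CRF and a serious adverse event form completed and submitted as described". The protocol does not say from what moment a pregnancy counts as having begun.

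Section 6.1.3 lists what an adverse event report must contain. The list includes the date and time of onset and the end date or duration. It does not include the date on which the site learned of the event.

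**The concern.** A site can act only on what it knows. When the limit is counted from onset, a slow disclosure uses up the time allowed before the site has had any chance to report. The last gap between assessments is about two months, against a limit of roughly a week and a half.

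Once the limit has lapsed, the protocol no longer says how quickly the site must report. The events already most delayed are therefore the ones left without an operative deadline. A site that reports the same day it hears of such an event is still out of compliance, and Section 6.1.5 asks for all deviations to be noted on the CRF. Because no awareness date is listed, the records would not separate a site that was slow from a site that was told late. Section 6.3 relies on the sponsor and the investigator recognising unacceptable risk, and prompt reporting after awareness is what serves that.

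For pregnancy there is a further difficulty: a clock that starts at the beginning of something whose beginning is not defined.

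**Working it through.** The protocol derives no figure on this point, so there is none to reproduce. The check is how often the stated limit has already expired when a scheduled visit first brings an event to light.

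**Inputs from the protocol.** Limit: 7 business days from onset (Section 6.1.2). Visits: 2 weeks, 1 month and 3 months, each ± 7 days (Section 6.2). Meditation arm: monthly group sessions after the core course (Section 5).

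**Assumptions.** Visits fall on days 14, 30 and 91. Onset is uniform over follow-up. The event is first learned of at the next visit and reported that same day. The assessment visits are the safety contacts. Public holidays are ignored.

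**Step 1: the limit in calendar days.** For onset on Monday through Sunday, 7 business days end 9, 9, 9, 11, 11, 10 and 9 calendar days later. The mean is 68/7 = 9.71 days.

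**Step 2: share overdue at discovery.** In a gap of g days, on average 9.71 onset days lie close enough to the next visit to be in time. The overdue share is (g − 9.71)/g.

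| Gap | g (days) | Overdue at discovery |
|---|---|---|
| Baseline to 2 weeks | 14 | 4.29/14 = 31% |
| 2 weeks to 1 month | 16 | 6.29/16 = 39% |
| 1 month to 3 months | 61 | 51.29/61 = 84% |
| All | 91 | (91 − 3 × 9.71)/91 = 61.86/91 = 68% |

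**Step 3: sensitivity.**

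- Fixed limit of 9 days: (91 − 27)/91 = 70%. Fixed limit of 11 days: (91 − 33)/91 = 64%.
- Visits moved by −7, 0 or +7 days: the lowest share is with visits on days 14, 30 and 84, (84 − 29.14)/84 = 65%. The highest is with visits on days 21, 23 and 98, (11.29 + 0 + 65.29)/98 = 78%.
- Length of the last gap: 91 − 30 = 61 days; with windows, from 84 − 37 = 47 to 98 − 23 = 75 days.
- Meditation arm with monthly sessions counted as contacts (days 14, 30, 60, 90): (90 − 4 × 9.71)/90 = 51.14/90 = 57%. With a further contact at day 7, standing for the core course, both 7-day gaps are wholly in time: (76 − 3 × 9.71)/90 = 46.86/90 = 52%.

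**Step 4: one case.** An event starts on day 42 and is disclosed on day 91, 49 days later. Its limit expired between day 51 and day 53, so it is 38 to 40 days overdue on discovery.

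**Step 5: pregnancy.** If the beginning means conception, the site has 9 to 11 calendar days from conception to report, which will rarely suffice. If it means diagnosis, the limit can be met when the subject tells the site promptly. The protocol supports neither reading over the other.

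**Step 6: clock started at awareness.** The share overdue at discovery is 0% by construction, and each event keeps its full 7 business days.

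**The case against.** The strongest reply is that visits are only one of three detection routes. Volunteered and observed reports also count, and the subjects are full-time staff of hospitals. A death, a hospitalization or a life-threatening event may well reach the study team long before a questionnaire visit. This stands. A reader might take 68% as the share of all serious events that will be reported late. The documents do not support that, because they give no basis for the split between routes.

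A reader might also infer that every pregnancy must be reported late. That needs the beginning to mean conception or earlier, which the protocol does not say. Nor are late-found events unknown to everyone: the subject often knows, and it is the site that does not. It also goes too far to say that the deadline and the visit schedule contradict each other. A promptly volunteered event can meet the limit, so this is a poorly chosen starting point and not an impossibility. Nothing in the text shows that sites would alter onset dates.

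Two further points have some force. Section 6.1.2 refers to a Schedule of Observations, while Section 6.2 is a schedule of outcome questionnaires that does not mention adverse events; treating its visits as the safety contacts is an inference. And Section 6.1.4 requires every serious event to be followed until it resolves or is judged chronic or stable, so a late-found event is not dropped. That rule governs follow-up, however, and sets no time for reporting.

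**Conclusion.** The point holds for serious adverse events first learned of at a visit. About two thirds of them (68%; 65% to 78% across the visit windows) are past the limit when the site learns of them. In the meditation arm the share falls to about 52% to 57% if the monthly sessions count as contacts. A majority is overdue in every variant tried, and no deadline then applies.

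The size rests on uniform onset, on the assessment visits being the safety contacts, and on same-day reporting at the visit. Any processing time would raise it. For pregnancy the conclusion is narrower: the same clock applies, but its starting point is undefined and has to be stated.

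The defect concerns the timeliness of safety reporting. It changes no endpoint, estimate or test. It is a rule the protocol states and fixes badly, not a detail it could have left to a statistical analysis plan.

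**What to change.** In Section 6.1.2, start the existing 7-business-day window on the day the investigator or study staff first become aware of the event. For pregnancy, start it on the day they first become aware of the pregnancy. In Section 6.1.3, add the awareness date beside the onset date on the Adverse Event CRF, so that timeliness can be checked. The length of the window remains the sponsor's choice.

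The cost is one amended sentence, with its clause for pregnancy, and one CRF date field. No visits, staff or subjects are added.
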